## Abstract

**Introduction:**

In recent years, the prevalence of infertility has significantly increased and has become a global reproductive health problem. The female ovarian reserves have been shown to decrease progressively with an increase in age. Besides, the rate of embryo implantation and clinical pregnancy also decreases. Traditional Chinese medicine has been widely applied in assisted reproductive technology. It is reported to have a significant influence on improving the quality of oocytes, improving endometrial receptivity, increasing clinical pregnancy rate, reducing pregnancy-related complications, etc. Therefore, this study will investigate the effect of Guilu Xian, a traditional Chinese medicine formula on IVF-ET outcome in older women with low prognosis.

**Methods and analysis:**

This trial is a prospective, multicenter, randomized double-blind clinical trial. A total of 120 infertile patients with low prognosis and receiving IVF or ICSI in 3 public hospitals in China will be randomly divided into two parallel groups: Guilu Xian group (*n* = 60) and placebo group (*n* = 60). Patients in both groups will be treated with antagonist regimens to promote ovulation, and all the patients will be required to take the medication from the 2nd to 4th day of the menstrual cycle to the day of egg retrieval. A comparison of the total number of oocytes obtained, the fertilization rate, clinical pregnancy rate, embryo quality, embryo implantation rate, and early spontaneous abortion rate between the experimental group and the placebo group will be performed.

**Trial registration:**

Chinese Clinical Trials Registry ChiCTR1900028255. Registered on 16 December 2019.

**Supplementary Information:**

The online version contains supplementary material available at 10.1186/s13063-021-05867-5.

## Introduction

Infertility affects about 8 to 12% of couples of childbearing age globally, and this accounts for more than 186 million people, and the majority of them being residents of developing countries. Increasing age in women is one of the most powerful negative predictors of fertility [1]. Rapid social and economic development has led to a gradual increase in the number of people with late marriages and childbearing, especially with the liberalization of the policy of “comprehensive second child.” This has increased in the number of older women seeking assisted reproductive technology (ART) treatment. The reproductive ability of women gradually decreases with increasing age [2]. Irreversible aging of the ovaries may lead to diminished ovarian reserves (DOR), however, in vitro fertilization-embryo transfer (IVF-ET) technology has become an effective treatment for DOR in older women. Although IVF-ET is increasingly being used to deal with infertility, the clinical pregnancy and live birth rate among older women with a poor ovarian response to exogenous gonadotropin stimulation (DOR) remains unsatisfactory.

Low prognosis is considered one of the most common and intractable problems of IVF-ET treatment occurring in about 47% of women. Out of these, 55% are women above the age of 35 years and with insufficient ovarian reserves [3–5]. The main cause of diminished ovarian response declines in the number of follicles responsive to FSH. This phenomenon is most common in older women with severely decreased ovarian reserves due to accelerated follicle loss [6]. However, in some cases, patients with good ovarian reserves may experience poor ovarian response owing to the gonadotropin dosage used [7] or due to the impact of genetic polymorphisms of endogenous gonadotropins and their receptors [8–10]. These factors change the response of recruitable follicles to exogenous gonadotropins, and this is associated with several problems such as a small number of eggs, poor embryo quality, poor pregnancy outcomes, etc. Therefore, patients with low prognosis are in need of high gonadotropin (Gn) dose and cycles for ovarian stimulation during the IVF cycle. This causes emotional and physical pain and financial burden to couples [6]. Currently, there are no effective ways of improving clinical pregnancy and live birth rates for patients with increased age and poor ovarian reserve [11]. The follicular fluid provides an important microenvironment in the growth and development of oocytes. Several metabolites in the follicular fluid are associated with the oocyte’s ability to undergo fertilization, embryonic development, and pregnancy outcome [12].

Traditional Chinese medicine has a significant effect on improving the quality of oocytes, improving the endometrial receptivity, increasing the clinical pregnancy rate, and reducing pregnancy-related complications. Tortoise deer erxian ointment, also known as tortoise deer erxian gum, was first recorded by Wang Sancai, a Chinese physician in the Ming Dynasty(1569). Guilu Xian reported the addition of turtle shell glue to the original “Guilu Erxian Ointment” and adjusted the dosage to strengthen the effect of nourishing yin and latent yang. The prescription is based on the tortoise shell glue and turtle shell glue as the main medicine, which functions in tonifying the kidney and as a nourishing essence and yin and latent yang. The application of deer horn glue is based on the fact that “those who are good at tonifying yin must seek yin in yang, then yin is born in yang, and the source of spring is not thirsty” [13]. This maximizes the tonifying effect in the balance of yin and yang. Therefore, Guilu Xian has the effect of tonifying the kidney essence, nourishing yin and latent yang, replenishing qi and nourishing spirit, and delaying aging. According to TCM theory, the pathogenesis of older women with low prognosis is deficient kidney essence, spleen qi deficiency, liver depression, and blood deficiency. “Tonifying the kidney, regulating the liver and invigorating the spleen” is the main treatment method, which corresponds to the tortoise deer fairy syndrome previously described. Recent studies have shown that TCM formula Guilu Erxian ointment has a good effect on the treatment of the reproductive system, and has an estrogenic effect [14–17]. However, there is no clear case on how to improve prognosis among older women. Therefore, there is necessary that a well-designed randomized controlled trial to confirm the effectiveness and safety of Guilu Xian in improving IVF-ET outcome in older women with low prognosis.

## Methods and analysis

### Aims of the study

To explore the effect of Guilu Xian, a traditional Chinese medicine formula on the IVF-ET outcome in older women with low prognosis.

### Trial design

This is a prospective, randomized, placebo-controlled, double-blind, superiority trial assigned in a 1:1 ratio. The study institutions were the Genetic and Reproductive Center of Traditional Chinese and Western Medicine, Affiliated Hospital of Shandong University of Traditional Chinese Medicine, the Second Affiliated Hospital of Shandong University of Traditional Chinese Medicine, and Jinan Central Hospital. The project leader regularly coordinates and communicates with each unit to understand the progress of the project and ensure the smooth progress of the project and the guarantee of quality. In order to ensure that there are enough participants, we will take measures such as providing free basic examinations, free drugs, and car allowance to better attract participants to join.

The inclusion criteria for this study will be patients aged between 35 and 42 years old, with insufficient ovarian reserve parameters (The POSEIDON criteria AFC < 5, AMH < 1.1 ng/mL) [18], and poor ovarian response (that is, the number of oocytes obtained after standard ovarian stimulation is less than 3). Patients should meet the diagnostic criteria of western medicine infertility, that is, women living without contraception for at least 12 months who are not pregnant are infertile [19].

The exclusion criteria are women with BMI ≥ 25 kg/m^2^; women who suffer from genetic diseases that are not suitable for childbearing as stipulated in the Maternal and Child Health Care Law; women with severe endometriosis, adenomyosis, and immune infertility; with untreated hydrosalpinx; with congenital or acquired abnormal development of the uterus and severe deformities of other reproductive organs; women with a history of endocrine dysfunction such as reproductive system tumor, thyroid dysfunction, and hyperprolactinemia; women receiving ovarian stimulation therapy or OCP in recent 3 months; women with a previous history of gynecological surgery such as the ovary; and all other contraindications of assisted reproductive technology.

The discontinuation criteria will be women who have adverse reactions such as nausea and obesity occurring during medication, women with no dominant follicular growth, early follicular ovulation, and no egg acquisition during ovarian stimulation. Three days after egg harvesting, the embryo was not formed.

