### Patient compliance

Assessment of patient’s compliance, including the bottle count of the drugs and weekly telephone follow-up, will be performed to find out if the participants are taking the medicine as agreed and any reasons for non-compliance. All unused drugs will be counted and registered. We will exclude patients with less than 70% compliance (i.e., in 40 days of treatment with Guilu fairy, while actually taking it for less than 28 days). They will not be included in the final analysis, but will be included in the intention-to-treat analysis.

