### Outcome measurement

The primary outcome will be the number of eggs obtained, and the secondary outcome will include the 2PN number, cleavage number, grade I embryo number, implantation rate, abortion rate, persistent pregnancy rate, trigger day ≥ 14 mm follicles, Gn days, and Gn.

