### Data analysis

All data are reported as mean ± standard deviation (SD). Patients with low adherence will not be included in the final analysis, but will be included in the intention-to-treat analysis. Two sets of analyses will also be performed for non-adherence and missing outcomes. The full analysis set (FAS) will include all patients who are randomized and will proceed according to the intention-to-treat principle. The protocol-compliant set will include all patients in the FAS who completed follow-up and did not experience a serious protocol violation.

For baseline comparisons, differences in means of continuous data between the placebo and intervention groups will be evaluated using independent Student’s *t* tests or Mann-Whitney *U* tests, depending on whether the data are normally distributed, and frequencies will be compared using chi-square tests. For longitudinal data with baseline, we will evaluate mean differences between and within groups using repeated measures analysis of covariance (ANCOVA). All tests will be two-tailed and ratios between the two groups will be compared using Fisher’s exact rate method with a significance level defined as a value < 0.05.

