### Supervision and management

We have also established a Data Monitoring Committee (DMC). The DMC is composed of the director of the Department of Reproductive Center of Shandong Provincial Hospital of Traditional Chinese Medicine as the chairman and the heads of the other two study sites as independent members. It is the responsibility of the DMC to monitor data, assess adverse events and cases of abnormal liver and kidney function results post-intervention on a regular monthly basis, review the core trial process, conduct interim analyses (the interim analysis includes the evaluation of the patient's follicular growth status, the number of retrieved oocytes and the incidence of adverse events. If the incidence of events of early follicular ovulation and absence of follicles after stimulation is as high as 30%, or the incidence of adverse events is as high as 10%, the trial will be terminated and the reasons for this will be analyzed.), and discuss relevant protocol amendments.

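### Low-yield events are discontinuation criteria although the egg count is the primary outcome, so the protocol-compliant set is selected on that outcome if discontinued women count as not having completed follow-up

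*Protocol article*

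**What the plan says.** Outcome measurement in the protocol article fixes the endpoint: "The primary outcome will be the number of eggs obtained".

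Trial design, in its discontinuation criteria, names absent growth of a dominant follicle, "early follicular ovulation, and no egg acquisition during ovarian stimulation". The same paragraph adds: "Three days after egg harvesting, the embryo was not formed".

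Data analysis defines two sets. The full analysis set (FAS) holds all randomized women under intention to treat. The protocol-compliant set holds "all patients in the FAS who completed follow-up and did not experience a serious protocol violation".

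Patient compliance treats intake on fewer than 28 of 40 days (below 70%) as low compliance. Of such women it says: "They will not be included in the final analysis, but will be included in the intention-to-treat analysis".

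Supervision and management foresees early ovulation and absent follicles. It ends the trial if their incidence reaches 30%.

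**The concern.** Failure to obtain an egg does not cause the primary outcome to be missing. It is the primary outcome, at value 0. Absent follicle growth and early ovulation also lead to a count of zero or close to it. When such events end a woman's participation and an analysis set then requires completed follow-up, membership of that set depends on the result being compared and not on adherence.

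What is at stake is the protocol-compliant comparison. If the drug lowers the share of zero-egg cycles, more women leave from placebo and the difference shrinks. If it raises counts but leaves that share unchanged, the difference grows. The two sets could then disagree for a reason that has nothing to do with compliance, and readers would take the disagreement for a compliance effect. Blinding and stratification by centre do not prevent this, because the selection happens after randomization.

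**Working it through.** **Chain of text.** Endpoint: egg count (Outcome measurement). Zero yield is a discontinuation criterion (Trial design). The compliant set needs completed follow-up (Data analysis). The secondary outcomes include implantation, abortion and persistent pregnancy, so follow-up runs past retrieval, and a woman stopped at or before retrieval would not ordinarily complete it. The article does not say that she does, or that she counts as 0. The step from discontinued to not having completed follow-up is therefore an inference.

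**Inputs.** The plan states no figure on this point to reproduce. From the documents: 60 women per arm, two-sided 0.05, planning values of 9 and 11 eggs (Estimation of the sample size). The documents give no egg distribution and no expected zero share, so everything else below is assumed.

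**Poisson illustration, only zero-egg women leave.** With mean m, the zero share is exp(-m) and the mean of those who stay is m / (1 - exp(-m)).

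For 2 (placebo) against 3 (Guilu Xian):
- Leaving: 60 × exp(-2) = 8.1 and 60 × exp(-3) = 3.0.
- Means of those who stay: 2 / 0.8647 = 2.313 and 3 / 0.9502 = 3.157.
- Difference: 3.157 - 2.313 = 0.844, instead of 1.00.
- Power (normal approximation): 0.859, instead of 0.934 with all women.

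| Assumed means | All women | Zero-egg women removed | Power, all / removed |
|---|---|---|---|
| 1.5 vs 2.5 | 1.00 | 0.793 | 0.972 / 0.890 |
| 2 vs 3 | 1.00 | 0.844 | 0.934 / 0.859 |
| 3 vs 4 | 1.00 | 0.917 | 0.833 / 0.788 |
| 4 vs 5 | 1.00 | 0.959 | 0.733 / 0.710 |
| 2 vs 4 | 2.00 | 1.762 | above 0.99 in both |
| 3 vs 5 | 2.00 | 1.877 | above 0.99 in both |
| 9 vs 11 | 2.00 | 1.999 | 0.934 / 0.934 |
| 2 vs 2 | 0 | 0 | no effect, no bias |

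**Variations at 2 vs 3.** With a negative binomial distribution (k = 2), the difference is 0.905 and power is 0.50 instead of 0.63. If women without a day-3 embryo leave as well, each egg giving an embryo with assumed probability 0.5 to 0.8, the difference is 0.83 to 0.85 and power 0.77 to 0.83.

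**Without a distribution.** Let q be the zero share and M the mean over all women in an arm. The difference among those who stay is M1 / (1 - q1) - M0 / (1 - q0).
- 9 vs 11, q = 10% on placebo and 5% on Guilu Xian: 11 / 0.95 - 9 / 0.90 = 11.579 - 10.000 = 1.58.
- 9 vs 11, q = 10% in both arms: (11 - 9) / 0.90 = 2.22.

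The true difference is 2.00 in both cases, so the distortion can go either way.

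**Extreme case.** Suppose the drug only prevents zero-egg cycles: 30% zeros on placebo, 10% on Guilu Xian, and 3 eggs on average among the other women in both arms. With all women the difference is 0.90 × 3 - 0.70 × 3 = 0.60. Among those who stay (42 and 54 of 60) it is 3 - 3 = 0.

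**The case against.** The strongest reply is that the decisive link is not written down. The article never says that a discontinued woman has not completed follow-up. A cancelled cycle is not a protocol violation, and her egg count is known. The day-3 embryo criterion is met after the egg count is fixed. The list can be read as reasons why a cycle stops before transfer. This stands as a limit on the point: the problem arises on the natural reading, not on the only possible one.

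A second reply is that such detail belongs in a full protocol or analysis plan. This succeeds only in part. The article itself fixes both the discontinuation criteria and the condition for entering the set, and it is their combination that is at issue.

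Three stronger readings are tempting, and the documents do not support them.
- A reader might infer that the intention-to-treat result is biased. The FAS contains all randomized women, so it is not selected by definition.
- A reader might infer that the headline result carries the selection, because Data analysis says "Patients with low adherence will not be included in the final analysis". That exclusion concerns intake below 70%. The article does not show that this final analysis is the protocol-compliant set.
- A reader might take 30% as the expected rate of such events. It is a stopping limit and says nothing about what is expected.

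It is also fair to say that the visible distortions rest on assumed low means or assumed zero shares. Low means are plausible, since entry requires fewer than 3 oocytes after standard stimulation, but the article states no expected mean of that size.

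**Conclusion.** The point holds in conditional form and is minor. If discontinued women are treated as not having completed follow-up, the protocol-compliant set is selected on the primary outcome, and its difference is distorted in either direction when the drug has an effect. If the drug has none, both arms lose the same expected share and no false-positive result arises by this route.

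The size cannot be known from the documents. It ranges from practically nil (Poisson, 9 vs 11) to about one sixth of the difference (0.84 of 1.00, Poisson, 2 vs 3). It is larger if the drug acts mainly on the chance of obtaining any egg.

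**What to change.** Three short additions to the protocol:

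- **Trial design:** *Absent follicle growth, premature ovulation, failure to obtain an egg and absence of a day-3 embryo stop the cycle or further treatment, but they are outcomes and not withdrawals. The woman stays in follow-up, and the number of eggs actually obtained is recorded: 0 if none is retrieved or no retrieval is done.*
- **Data analysis:** *None of these events by itself removes a woman from the FAS or the protocol-compliant set.*
- **Patient compliance:** *For a woman whose cycle stops early, compliance is judged against the days of intake scheduled up to that stop.*

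The third addition is needed because the 70% rule could otherwise remove the same women by another route. For example, a woman who took every dose until a stop on day 14 would score 14 / 40 = 35% and be excluded because of her outcome. The wording about stopping the cycle or further treatment is deliberate: the Abstract ends medication on the day of retrieval, whereas Intervention gives 40 days, so a day-3 embryo failure may come when there is no treatment left to stop.

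The cost is a few sentences, with no extra patients or procedures. The downside is a few more zero counts in the protocol-compliant set.

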### Technical route

See Annex 1 for details.

### Schedule of the study process

See Annex 2 for details.

### Case registration and allocation

The clinicians being involved in the study will record the basic AFC and AMH values of the patients after obtaining informed consent from the participants. Upon meeting the inclusion criteria, the patients will be randomly distributed in groups with the order of registration, and the clinicians are responsible for recruiting patients in sequence and will use case questionnaires to record their identity, age, and other basic information.

The clinicians will give medication to participants within 3 days after screening. Data will be recorded on drug distribution and use, and timely reports provided to the clinicians on the drug dose and patients’ discomfort during the process.

This study will include 120 patients who will be recruited and randomly divided into two groups using the R language version 3.5.1: the elderly test group and the elderly control group. Sixty, patients will be treated with Guilu Xian and 60 with the placebo. The elderly and the experimental group will be treated with an antagonist, and the tortoise deer fairy and placebo will be administered from the third day of menstruation before IVF.

### Ovarian stimulation and egg extraction and transplantation

The flexible GnRH antagonist regimen will be utilized in the COS regimen in both groups. On day 3 of the cycle, gonadotropin (Serono) or urinary gonadotropin (Lubao biochemical Pharmaceutical Company, Zhuhai Lizhu Group) 300 IU will be administered, and regular monitoring of follicular development performed. When ≥ 1 dominant follicle is at least ≥ 14 mm in diameter or LH 10 U/L, GnRH-ant will be administered. However, when ≥ 2 dominant follicles are ≥ 18 mm in diameter, urogenic hCG 8000~10,000 U or r-hCG 250 μg will be administered. Transvaginal ultrasound-guided paracentesis will be performed 36 h after the injection of HCG. Fresh or frozen embryo transfer will be based on the patient’s characteristics such as intima growth value, *P* value, and embryo score. Following transplantation, progesterone will be injected into the supporting luteal muscle at 40 mg/ day or application of progesterone vaginal sustained-release gel at 90 mg/day. Drug administration will be stopped from the day of transplantation to the 10th week of gestation.

### Estimation of the sample size

In a recent study in China, it was reported that in conventional IVF or ICSI, the total number of retrieved eggs in the treatment group (259.77±25.45) was significantly higher than that in the placebo group (235.59±26.44). In this study, the number of eggs obtained in the Guiluxian group was 11 under the original hypothesis and 9 under the alternative hypothesis (9 in the placebo group). The bilateral *Z* test of the combined variance will be used to estimate the sample size at 0.05 level of significance. The ratio between groups will be1:1. The minimum sample size found for each group is 49 people, hence a total of 98 people. Besides, 90% of the detection ability will be obtained, and the difference in ratio between groups is 0.15. Considering a dropout rate of 15%, we will be expected to enroll 120 participants, with 60 participants in each group (see supplementary files 1 and 2 for details).

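### The sample size assumes 9 eggs on placebo, but eligibility requires fewer than 3 oocytes and AFC below 5, so the stated 90% power is unsupported for the women enrolled

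*Protocol article*

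**What the plan says.** Under Outcome measurement: "The primary outcome will be the number of eggs obtained". Under Estimation of the sample size, the planning value for the active arm reads "the number of eggs obtained in the Guiluxian group was 11 under the original hypothesis". The value set against it, with the two hypothesis labels apparently reversed, is "9 under the alternative hypothesis (9 in the placebo group"). The test is a two-sided Z test with pooled variance "at 0.05 level of significance". The stated result is 49 per group for 90% power, raised to 60 per group (120 in all) for 15% dropout.

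The only SDs printed come from an earlier study in conventional IVF or ICSI. They are 25.45 around 259.77 in its treated arm and 26.44 around 235.59 in its control arm; the treated value is said to be one that "was significantly higher than that in the placebo group (235.59±26.44"). No low-prognosis restriction is mentioned for that study.

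Under Trial design, women must be aged 35 to 42, "with insufficient ovarian reserve parameters (The POSEIDON criteria AFC < 5, AMH < 1.1 ng/mL"), and have a poor ovarian response, meaning that "the number of oocytes obtained after standard ovarian stimulation is less than 3".

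**The concern.** The sample-size section and the inclusion criteria describe different women. A placebo mean of 9 is more than three times the oocyte count that makes a woman eligible, and nearly twice the AFC limit. The Introduction itself links poor ovarian response with a small number of eggs.

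Power for a comparison of means depends on the difference and the SD. Both were presumably chosen for a population averaging 9 to 11 eggs, and neither can be assumed to carry over to women selected for a very low yield. What is at stake is how the result is read. A null finding from a trial described as having 90% power would be taken as evidence against an effect, although the protocol gives no basis for saying which effect the trial can detect in these women.

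**Working it through.** **Inputs from the protocol.** Means 11 and 9 (difference 2, ratio 11/9 = 1.22); two-sided alpha 0.05; power 90%; 49 per group; 60 per group enrolled; 15% dropout. After dropout, 60 × 0.85 = 51 evaluable per group. I take 9 and 11 as eggs per woman, the only workable reading.

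**1. The plan's own figure.** With n per group = 2 × (1.960 + 1.282)² × SD² / difference² and (1.960 + 1.282)² = 10.507:
- Cited study: difference 259.77 − 235.59 = 24.18, pooled SD = √((25.45² + 26.44²)/2) = 25.95. n = 2 × 10.507 × 25.95² / 24.18² = 24.2, so 25 per group, not 49.
- Difference 2 with that SD: n = 2 × 10.507 × 25.95² / 2² = 3538 per group.
- Back-solving 49 per group for a difference of 2: SD = 2 × √(49/2) / 3.2415 = 3.05.

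So 49 is not reproduced from the printed inputs. It needs an SD of about 3.05, which is not printed. The dropout step is adequate: 98 / 0.85 = 115.3, so 116, and 120 covers it.

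**2. Planning mean against eligibility.** 9 / 3 = 3, and eligible women had fewer than 3, so the ratio exceeds 3. Against the AFC limit, 9 / 5 = 1.8.

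**3. Power under stated assumptions.** The protocol gives no mean or SD for eligible women. I assume a placebo mean of 2 to 4, SD 1.5 to 2.5, and a two-sided t test with 51 per group.

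*If the relative effect 11/9 carries over* (difference = mean × 2/9):

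| Placebo mean | Difference | SD 1.5 | SD 2 | SD 2.5 |
|---|---|---|---|---|
| 2 | 0.44 | 32% | 20% | 14% |
| 2.5 | 0.56 | 46% | 28% | 20% |
| 3 | 0.67 | 60% | 39% | 27% |
| 4 | 0.89 | 84% | 60% | 43% |

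*If the full 2-egg gain holds:* power is above 99% at SD 1.5 and 2, and 98% at SD 2.5. A gain of 2 is 2/3 = 67% on a mean of 3, and 2/2 = 100% on a mean of 2.

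*If the SD shrinks in proportion to the mean* (3.05 × 2/9 = 0.68 at a mean of 2; 3.05 × 4/9 = 1.36 at a mean of 4), the 11/9 effect keeps about 90% power.

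**4. Detectable difference with 120 enrolled.** With 51 per group at 90% power, difference = SD × √(2 × 10.507 / 51) = 0.642 × SD, that is 0.96, 1.28 and 1.60 oocytes for SD 1.5, 2 and 2.5.

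**The case against.** The strongest reply is that the protocol states two means, and hence an absolute difference of 2 eggs. It never states a 22% relative effect. If the 2-egg difference is kept with the smaller SDs assumed here, power exceeds the stated 90%. This stands. A reader might infer from the mismatch that the trial is underpowered, that the effect shrinks to about half an egg and that it would usually be missed. The documents do not support that. The half-egg figure follows only from carrying the ratio over to a mean of 2 to 3, and even then power reaches 60% at one end of the range. A reader might also attribute the implied SD of about 3 to normal responders. The protocol prints no SD on this scale and gives no source for one.

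Other points have partial force:
- The count below 3 presumably comes from an earlier cycle, and women selected for a low count may do better in the trial cycle. Hence the row for a mean of 4. Nothing shown explains a mean of 9.
- The comma between the AFC and AMH limits could be read as either/or. The oocyte criterion is joined by *and*, so the conflict remains.
- If all 60 per group yield outcomes, as the full analysis set intends, the 14% to 60% range becomes 16% to 68%.
- Supplementary files 1 and 2 are cited for details and are not shown. They may hold the SD and the origin of 9 and 11, but they cannot make a printed placebo mean of 9 fit the printed eligibility criteria.

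**Conclusion.** The point holds as a contradiction between stated figures: the mean used for planning does not fit the women whom the criteria admit, so 90% power cannot be claimed for them. That conclusion needs no outside data.

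Its size cannot be settled from the protocol. Across the assumptions tabulated, power runs from 14% to above 99%, depending mainly on whether the effect is relative or absolute and then on the SD. The high end requires a 2-egg gain that would raise a mean of 2 to 3 by 67% to 100%, for which the protocol offers no support. The low end requires an assumption about the relative effect that the protocol does not make either. Confidence is high that the stated power is unsupported, and low for any single replacement value.

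**What to change.** In the sample-size section:

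1. Replace 9 and 11 with a placebo mean and SD that fit women meeting the inclusion criteria, for example from the three centres' past cycles if such records are available, and name the source.
2. State the assumed effect as an absolute difference in oocytes, and print the SD used.
3. Replace the 90% claim with the difference detectable with 120 women. At 90% power with 51 per group this is about 1.0, 1.3 or 1.6 oocytes for SD 1.5, 2 or 2.5.
4. Say that a null result will be read against that restated difference.

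The cost is a search of existing data, where it exists, and a rewritten paragraph; no patients are added. The drawback is that the stated power may become less favourable. Recruitment was due to start on 15 October 2020, so the gain is mainly in honest reporting: rewriting the paragraph would not cure a real shortfall in power.
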